1.1. Roles and Responsibilities

The Bangkok Tenofovir Study Group and Bangkok Metropolitan Administration

- Collaborate in protocol development and logistics of study procedures
- Submit protocol to Ethical Review Committees of the BMA, and the Thailand Ministry of Public Health
- Train clinic staff in study procedures and counseling
- Screen and obtain written informed consent from participants
- Enroll participants, provide study drug, and arrange follow-up
- Perform data and specimen collection and counseling
- Perform urine testing for pregnancy
- Evaluate, treat, and refer HIV infected study participants
- Provide secure, private clinic space for evaluation and counseling of participants.

*Thailand Ministry of Public Health – U.S. CDC Collaboration*

- Develop full protocol with input from collaborators
- Submit protocol to the United States CDC Institutional Review Board for approval
- Assist in training clinic staff in study procedures and counseling
- Provide study materials including questionnaires, study forms, office supplies, specimen collection materials and laboratory equipment
- Handle specimens and perform laboratory testing as defined in protocol
- Perform data management
- Monitor trial data and study staff performance
- Perform data analysis, interpretation, and communication of results with input from collaborators

*Thailand Ministry of Public Health*

- Collaborate in protocol development
- Facilitate communication with MOPH Ethical Review Committee
- Assist with data and laboratory analysis and interpretation and communication of results

*Division of HIV/AIDS Prevention-Surveillance and Epidemiology, Epidemiology Branch, Centers for Disease Control and Prevention*

- Collaborate in protocol development and logistics of study procedures
- Facilitate communication with CDC Institutional Review Board and CDC consultants
- Assist with development of data collection instruments, data and laboratory analysis and interpretation and communication of results
- Provide financial support to both BTSG and TUC to prepare for and to conduct the Bangkok Tenofovir study as described in the protocol

**2. Protocol Summary**

**Title:** Study of the Safety and Efficacy of Daily Tenofovir to Prevent HIV Infection Among Injection Drug Users in Bangkok, Thailand (Bangkok Tenofovir Study)

**Objectives:** Primary objectives:

- To determine if daily oral tenofovir 300 mg prevents HIV infection among injection drug users (IDUs) in Thailand
- To determine if daily oral tenofovir 300 mg is safe when given to HIV-uninfected IDUs in Thailand

Secondary objectives:

- To evaluate changes in HIV associated risk behaviors during the trial
- To evaluate adherence of IDUs to daily tenofovir/placebo
  - - To determine if daily tenofovir is associated with a lower HIV viral load set point or higher CD4 count among trial participants who become HIV infected
    - To determine if tenofovir is associated with the development of antiretroviral resistance among trial participants who become HIV infected
    - To determine if the genetic characteristics of HIV viruses that infect placebo recipients differ from HIV viruses that infect tenofovir recipients

**Design:** A phase II/III, randomized, double-blind, placebo-controlled study of the efficacy and safety of oral tenofovir (tenofovir disoproxil fumarate) 300 mg administered once daily to HIV-uninfected IDUs.

In phase II, IDUs will be randomized 1:1 to once daily tenofovir or placebo until 200 person-years of observation have accrued when a data safety monitoring board (DSMB) safety review will be done. If safety is confirmed, all phase II participants will continue, and additional participants will be enrolled into the phase III trial until 2,400 persons have been enrolled. Participants will choose between daily follow-up with directly observed therapy (DOT) or monthly follow-up. Participants will remain on assigned study medication until 40 endpoints have accrued.

**Population:** HIV-uninfected Thai IDUs ages 20-60 years.

**Study Sites:** The study will be conducted at 17 Bangkok Metropolitan Administration (BMA) drug treatment clinics located in Bangkok, Thailand.

**Duration:** Phase II/III is estimated to take 48months; 36months to enroll 2,400participants, and an additional 12 months to complete follow-up.

**Test Products:** Tenofovir 300 mg or placebo.

**Study Procedures:** Interviews, risk reduction counseling, physical examinations, and/or laboratory evaluations at screening, enrollment, and every 4 weeks while on tenofovir or placebo.

**Endpoints:** HIV seroconversion, adverse events, rates of injecting and needle sharing, adherence to study drug/placebo, HIV viral load and CD4 counts, antiretroviral resistance, and genetic characteristics of infecting HIV viruses.

**Eligibility Criteria:** Potential participants must be age 20-60 years, HIV-uninfected, report injection drug use during the 12 months before trial enrollment, be capable of providing blood, oral secretions and urine, understand the protocol procedures, and provide written informed consent.

3**. Abbreviations and acronyms**

ACASI audio computer assisted self-interview

AE adverse event

AIDS acquired immunodeficiency syndrome

ALT (SGPT) alanine aminotransferase

ART antiretroviral therapy

AST (SGOT) aspartate aminotransferase

β-HCG β-human chorionic gonadotropin

BMA Bangkok Metropolitan Administration

BMD bone mineral density

BTSG Bangkok Tenofovir Study Group

BVEG Bangkok Vaccine Evaluation Group

CBC complete blood count

CD4 cluster of differentiation 4

CDC U.S. Centers for Disease Control and Prevention

CRC Community Relations Committee

CRF case report form

dL deciliter

DOT directly observed therapy

DSMB data safety monitoring board

EDTA Ethylene diamine tetra-acetic acid

EIA enzyme immunoassay

ERC Ethical Review Committee

Extension Study Extended follow-up of participants in the phase III trial of AIDSVAX B/E HIV vaccine

FDA Food and Drug Administration

g gram(s)

GCP Good Clinical Practice guidelines

HAART highly active antiretroviral therapy

HBV hepatitis B virus

HIV-1 human immunodeficiency virus, type 1

HPLC high performance liquid chromotography

ICH International Conference on Harmonization

IDUs Injection Drug Users

IRB Institutional Review Board

IU international unit(s)

kg kilogram(s)

LLN lower limit of normal

MCH maternal and child health

mg milligram(s)

mL milliliter(s)

mm3 cubic millimeter(s)

MOPH Thailand Ministry of Public Health

NNRTI non-nucleoside reverse transcriptase inhibitor

NRTI nucleoside reverse transcriptase inhibitor

NtRTI nucleotide reverse transcriptase inhibitor

PBMC peripheral blood mononuclear cells

PCR polymerase chain reaction

PEP post-exposure prophylaxis

PI protease inhibitor

po by mouth

PrEP pre-exposure prophylaxis

QA quality assurance

QC quality control

RT reverse transcriptase

RTI reverse transcriptase inhibitor

SAE serious adverse event

SIV simian immunodeficiency virus

SST serum separator tube

TDF Tenofovir Disoproxil Fumarate

TUC Thailand MOPH – U.S. CDC Collaboration

µg microgram(s)

ULN upper limit of normal

VAX003 Phase III trial of AIDSVAX B/E HIV vaccine

WB Western Blot

**5. Introduction**

**5.1 Project justification**

In Thailand, the HIV epidemic began among IDUs in 1988, with the prevalence rising from less than 1% to more than 40% in 1 year.1 As part of a national plan to develop and evaluate HIV vaccines,2 a cohort study of 1,209 IDUs was conducted from 1995–1998 in Bangkok.3 The study was conducted at 17 drug treatment clinics of the BMA. Each year, approximately 8,000-10,000 IDUs are treated at BMA drug treatment clinics. Treatment regimens include 45-day methadone detoxification and methadone maintenance.

Among IDUs screened for the cohort study, 29.9% were HIV-seropositive. The HIV incidence rate was 5.8 per 100 person-years; 88.2% of eligible participants returned for follow-up visits at 12 months, 75.9% at 24 months, and 71.2% at 36 months. The successful planning and conduct of this cohort study contributed important background data and research infrastructure that lead to the first phase III HIV vaccine trial in Asia.From March 1999 – August 2000, 4,943 IDUs were screened for enrollment in the AIDSVAX B/E HIV vaccine trial; their median age was 26 years, 94.3% were male, and 34.2% were HIV-seropositive.4 Among the 2,545 IDUs who enrolled in the vaccine trial, 93.8% reported injection drug use during the 6 months before enrollment. The frequency of drug use was high, with 39.4% reporting use daily and 32.7% at least weekly. The annualized HIV incidence rate during the 3-year trial (i.e., 1999 – 2003) was 3.4 per 100 person-years, varying from 2.1 to 4.2 during the course of the trial with no clear temporal trend (unpublished data).

During the vaccine trial, HIV education and risk-behavior counseling were provided at every study visit according to a standard operational protocol. Reports of injection drug use and needle sharing decreased significantly during the vaccine trial.5 The use of condoms and bleach to clean injection equipment were provided free of charge at every visit. Consistent with Thailand’s HIV prevention policy, drug injection equipment was not provided or exchanged at participating clinics, but sterile syringes and needles are readily available without prescription at pharmacies for 8 Thai baht (about US$0.20). Despite frequent, client-centered counseling, HIV incidence remained above 3% per year during the vaccine trial.

Based on population estimates6 and data from the AIDSVAX B/E vaccine trial, approximately 1,000 IDUs are infected with HIV each year in Bangkok. The number of candidate HIV vaccines in clinical trials has increased in recent years.7 Nonetheless, an effective preventive HIV vaccine is still years away and there is an urgent public health need to find other HIV prevention tools, particularly for those who are unable or unwilling to respond to currently available behavioral interventions. Tenofovir, a once-daily antiretroviral with low toxicity and slow development of resistance mutations, may be such a prevention tool.

**5.2 Why tenofovir?**

There is ample evidence in animals and humans that post-exposure prophylaxis, if given promptly, can reduce the risk of acquiring HIV infection. In the case of health care workers with needle-stick injuries from HIV-infected patients, zidovudine monotherapy is estimated to reduce the risk by 81%.8 It is biologically plausible and consistent with data from both perinatal HIV prevention studies and other infectious diseases that pre-exposure prophylaxis (PrEP) would be at least as effective and likely more so.

Suggested criteria for an ideal PrEP agent include the following:9

- Potent antiretroviral drug
- Rapidly bioavailable and long duration of action
- Easily administered on a once-daily or less dosing schedule
- Demonstrated low rates of clinical toxicity and hypersensitivity and well tolerated
- Favorable drug interaction profile for commonly used medications
- High “genetic barrier” to the emergence of drug resistance
- Affordable

Tenofovir meets all these criteria and in animal studies, it has shown the ability to protect non-human primates against intravenous, oral, and mucosal simian immunodeficiency virus (SIV) challenge.10 In addition, tenofovir is approved for use in treating persons with HIV infection in both the U.S. and Europe, has minimal drug-drug interactions, and few clinical contraindications.

**5.3 Why a phase II safety study?**

While multiple phase I and II studies have been done to assess the safety, tolerability, and pharmacokinetics of tenofovir for treatment of HIV infection, there are limited data on tenofovir use among HIV-uninfected persons. A study of 14 HIV uninfected subjects on stable doses of tenofovir showed that tenofovir 300 mg once daily did not affect the pharmacodynamics or pharmacokinetics of methadone.11 Nonetheless, additional safety data are needed to ensure tenofovir can be safely used by IDUs.

**5.4 Potential increase in HIV associated risk behavior**

In populations being studied for PrEP and other HIV prevention strategies (e.g., vaccines, microbicides), concerns have been raised about increased HIV associated risk behavior. It is possible that study participants will, despite education otherwise, believe that they are protected by the study medication and continue or increase risk behaviors. However, data available from previous studies in this IDU population suggest that HIV associated risk behaviors will decline.3,5 Active community participation will be sought to ensure appropriate risk reduction messages are presented to study participants.

**5.5 Tenofovir adherence**

HIV-infected participants in the AIDSVAX B/E HIV vaccine trial were offered ART. Data from the vaccine trial and published research suggest that IDUs in Bangkok will adhere to daily oral medications.12,13 Clinic staff will observe participants who choose daily follow-up take their daily dose of tenofovir (directly observed therapy – DOT). Active community participation will be sought to ensure appropriate adherence messages are presented to study participants. Adherence counseling will be refined based on input from the community.

**6. Study objectives**

**6.1 Primary objectives**

- To determine if daily oral tenofovir 300 mg prevents HIV infection among IDUs
- To determine if daily oral tenofovir 300 mg is safe when given to HIV-uninfected IDUs

**6.2 Secondary objectives**

- To evaluate changes in HIV associated risk behaviors during the trial
- To evaluate adherence of IDUs to daily tenofovir/placebo
  - - To determine if daily tenofovir is associated with a lower HIV-1 viral load set point or higher CD4 count among trial participants who become HIV infected
    - To determine if tenofovir is associated with the development of antiretroviral resistance among trial participants who become HIV infected
- To determine if the genetic characteristics of HIV viruses that infect placebo recipients differ from HIV viruses that infect tenofovir recipients

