**7.2 Secondary endpoints**

Changes in HIV associated risk behaviors will be measured by:

- Rates of reported injection drug use and injection drug use frequency during the trial
- Rates of reported needle sharing
- The number of unprotected sexual acts over the course of the trial
- Number of reported sexual partners over the course of the trial
- Proportional use of condoms during sexual intercourse

Medication adherence will be measured as:

- Rates, by interview and documentation on tenofovir adherence card, of participants taking at least six (86%) of seven daily doses of study drug each of the four weeks preceding the monthly study visit

Differences in virologic and immunologic responses to HIV infection among tenofovir and placebo recipients will be measured by:

- Plasma viral load, measured by quantitative RNA PCR, a predictor of clinical progression of HIV disease;14 CD4 cell counts will be measured by flow cytometry
- Rates and nature of HIV antiretroviral genotypic and phenotypic resistance will be measured
- Genetic characteristics of infecting HIV viruses including DNA sequence analysis and antibody binding studies will be conducted

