**10.3.7 HIV and additional testing in scheduled and exit visits**

If OraQuick test of oral fluid is non-reactive, the participant will be informed that there is no evidence of HIV infection. In order to ensure that daily oral tenofovir does not lead to OraQuick non-reactive test results among HIV-infected volunteers, HIV confirmatory nucleic acid testing (NAT) will be done on sera available from volunteers who test OraQuick non-reactive.

If OraQuick HIV testing is reactive, study medication will be stopped, and the participant will be informed that the test is reactive and that blood tests are required to confirm the result. If the participant agrees**,** blood will be drawn and confirmatory testing done (i.e., EIA and, if necessary Western Blot) and the participant will complete the risk assessment and adherence questionnaire.

At the follow-up visit in 2 weeks, participants will receive post-test counseling and results of confirmatory testing. Participants, who test positive on confirmatory HIV testing, will have HIV-1 viral load, HIV-1 genetic characterization, antiretroviral drug resistance and CD4 testing and will be referred for follow-up care. Participant specimens from previous visits will be tested to determine if the participant was in the HIV window period when they previously tested HIV negative by oral fluid testing.

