**13.2 Effectiveness outcome**

Efficacy analysis is designed to determine if tenofovir efficacy to prevent HIV infection exceeds a threshold level of 10%. A lower threshold of 10% was selected in order to provide a result that can guide public health actions. HIV incidence during the AIDSVAX B/E HIV vaccine trial was 3.4 per 100 person-years. We suspect HIV incidence among IDUs in Bangkok has declined due to HIV prevention activities of BMA drug treatment clinic staff and changes in drug use (i.e., less heroin, more midazolam and methamphetamines)5. In order to ensure that there is sufficient power to achieve the study’s primary objective, to determine if tenofovir prevents HIV infection, we will use an endpoint-driven study design. Based on simulations assuming tenofovir efficacy of 50%, 67%, and 90% and a 1-tail alpha of 0.025, we determined power to provide a result with a lower limit 95% CI > 10% (Table 4).

Table 4. Power to demonstrate tenofovir efficacy with 95% CI >10%

| Estimated Tenofovir Efficacy | Expected Endpoints by Group | | | Power to show tenofovir efficacy with lower limit 95% CI > 10% |
| --- | --- | --- | --- | --- |
| Tenofovir | Placebo | Total |
| 50% | 12 | 24 | 36 | 37% |
| 67% | 9 | 27 | 78% |
| 90% | 3 | 33 | 99% |
| 50% | 13 | 27 | 40 | 49% |
| 67% | 10 | 30 | 82% |
| 90% | 4 | 36 | 99% |
| 50% | 14 | 30 | 44 | 54% |
| 67% | 11 | 33 | 86% |
| 90% | 4 | 40 | >99% |

If tenofovir efficacy is 67%, we have 82% power to demonstrate at least 10% tenofovir efficacy with 40 endpoints. A human post-exposure prophylaxis study suggests tenofovir efficacy to prevent HIV infection will exceed 67%.8

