**13.9 Efficacy analysis**

The study hypothesis is that HIV incidence will be lower among participants receiving tenofovir than among participants receiving placebo. A log-rank statistic will be used to test the efficacy of treatment.25 The efficacy of treatment will be estimated as

Efficacy = 1 – *RR*

where *RR* is the hazard ratio estimated from a discrete time proportional hazards regression model with an indicator variable representing treatment arm. Confidence intervals for efficacy can be calculated using the confidence limits for the *RR*.

All analyses will be performed on an intention-to-treat basis. Rates of HIV seroconversion with Poisson 95% exact confidence intervals will be used to summarize the data. Discrete time proportional hazards regression will be applied to adjust the treatment effect for age and gender and for other demographic or behavioral variables, which, despite the randomization, were heterogeneously distributed between the study arms.

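### Set point, CD4 count and resistance are compared only among infected participants, a group tenofovir is expected to change, so the contrast is not randomised and could show a difference with no drug effect on the virus

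*Protocol*

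**What the plan says.** Two secondary objectives in protocol section 6.2 are defined within the infected. One is to determine whether "daily tenofovir is associated with a lower HIV-1 viral load set point or higher CD4 count among trial participants who become HIV infected". The other reads "To determine if tenofovir is associated with the development of antiretroviral resistance among trial participants who become HIV infected". Section 7 repeats the restriction. Section 7.2 presents the endpoints as a contrast between arms: "Differences in virologic and immunologic responses to HIV infection among tenofovir and placebo recipients will be measured by" plasma viral load, CD4 count, resistance and genetic characteristics of the virus.

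The measurements exist only for that group. Section 10.3.7 states: "Participants, who test positive on confirmatory HIV testing, will have HIV-1 viral load, HIV-1 genetic characterization, antiretroviral drug resistance and CD4 testing". Appendix C likewise lists these tests for seroconverters only.

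The plan also expects the drug to change who is in the group. Section 13.9 says: "The study hypothesis is that HIV incidence will be lower among participants receiving tenofovir than among participants receiving placebo". Section 13.2 adds: "If tenofovir efficacy is 67%, we have 82% power to demonstrate at least 10% tenofovir efficacy with 40 endpoints", and the matching row of Table 4 expects 10 tenofovir and 30 placebo infections.

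Sections 13.7 and 13.9 adjust for baseline variables that turn out unevenly distributed between the study arms. No section mentions selection through infection.

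**The concern.** Randomisation makes the two full arms comparable. It does not make the infected members of each arm comparable when the drug prevents some infections and not others. The placebo group contains every infection that occurs without the drug. The tenofovir group contains those that occurred in spite of it, or because it was not taken. If size of inoculum, viral fitness, host factors or adherence affect both who is protected and the later viral load, the groups differ for reasons unrelated to any drug effect on the virus. Adjusting for imbalances between the randomised arms does not remove this, because the selection happens later.

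At stake is the reading of three secondary results. A lower or higher set point, a CD4 difference, or a higher share of resistant virus on tenofovir could be taken as a drug effect when part or all of it is selection. Resistance matters most, since section 11.1 lists it among the risks to participants.

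**Working it through.** **Inputs from the protocol.** 40 endpoints, 67% efficacy, 10 v 30 infections, 82% power, a 10% efficacy threshold and a "1-tail alpha of 0.025" (section 13.2, Table 4); 1:1 allocation (13.4); general significance level 0.05 (13.7).

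**Assumptions, not in the protocol.** Set-point SD 0.7 to 1.0 log10; odds of breakthrough rising 1.5- to 3-fold per log10 of set point; a two-sided t-test, because no test is named for these endpoints.

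**1. Reproduce the plan's figure.** Given 40 events, the tenofovir count is Binomial(40, HR/(1+HR)). At HR 0.33 the probability is 0.33/1.33 = 0.248, which gives an expected split of 9.9 v 30.1 (plan: 10 v 30). At the threshold HR of 0.90 the probability is 0.90/1.90 = 0.474. The largest count with a lower-tail probability of at most 0.025 is 12 (0.0195; 13 gives 0.0411). Power is P(X ≤ 12 | 0.248) = 82.8%, against 82% stated. The 10 v 30 split is a sound basis for what follows.

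**2. Fraction that breaks through.** 10/30 = 1/3. About two thirds of the people who would be infected on placebo are absent from the infected tenofovir group.

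**3. Spurious difference with no drug effect on the virus.** Let set point Y be normal among those infected on placebo. Let the probability of breakthrough be 1/(1 + exp(−(a + bY))), with b = ln(odds ratio per log10) and a chosen so that the average is 1/3. The artefact is the mean of Y among breakthroughs minus the overall mean, in log10:

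| Odds ratio per log10 | SD 0.7 | SD 0.8 | SD 1.0 |
|---|---|---|---|
| 1 (no selection) | 0 | 0 | 0 |
| 1.5 | 0.13 | 0.17 | 0.26 |
| 2 | 0.22 | 0.28 | 0.42 |
| 3 | 0.32 | 0.41 | 0.60 |

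If breakthrough favours low set points instead, the same sizes apply with the sign reversed.

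**4. False-positive rate at a nominal 5%, 10 v 30.** With SD 0.8 and odds ratios of 1.5, 2 and 3, it is about 9%, 15% and 27% (noncentral-t approximation). With SD 1.0 it is about 11%, 20% and 37% (simulation). With no selection it stays at 5%.

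**5. Worst case.** If breakthroughs are exactly the top third of Y, the shift is φ(z)/q with q = 1/3 and z = 0.431: 0.3636/0.3333 = 1.09 SD. That is 0.76, 0.87 or 1.09 log10 at SD 0.7, 0.8 or 1.0. The same formula gives 0.80 SD at 50% efficacy and 1.75 SD at 90%.

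**6. Scale.** The difference detectable with 80% power is 2.80 × √(1/10 + 1/30) = 1.02 SD, or 0.82 log10 at SD 0.8. The worst-case artefact slightly exceeds it.

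**7. Resistance.** The figures above do not quantify this limb. A hypothetical shows the issue: 2 resistant of 10 infections against 3 of 30 reads as 20% v 10%. With equal person-years the tenofovir arm nevertheless has fewer resistant infections, 2 against 3. The choice of denominator reverses the conclusion.

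**The case against.** The best defence is that set point has no meaning without infection, so an infected-only contrast is unavoidable. Section 6.2 speaks only of association, and section 13 fixes no test, model or decision rule for these endpoints. The detail may sit in an analysis plan that is not shown. This stands in part: the absence of a method is not the point. The point is the comparison group written into the objectives, with nothing to say that it is conditional on infection.

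A reader might infer that the protocol commits to an infected-only resistance proportion. It does not. Section 7.2 speaks of rates, and section 14.2 asks interim reports for the number, percent and rate of secondary outcomes alongside accumulated follow-up. A person-year rate fits that reporting; the protocol simply does not say which measure carries the comparison.

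A reader might also infer that the set-point comparison is certainly biased. The documents do not support that. The SD and the strength of selection are assumptions, and without selection the test keeps its level. Section 9.5 also plans tenofovir levels around seroconversion in tenofovir recipients, which helps separate non-use from true breakthrough.

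Finally, one might want a drug effect claimed only when the selection bounds exclude zero. That is too strict to require here. In simulations with SD 0.8, no selection and a true effect of 0.82 log10, the point bounds exclude zero in about 47% of trials, against about 78% rejection by the t-test.

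**Conclusion.** The concern holds as a limit on interpretation. The set-point, CD4 and resistance objectives rest on a group formed after randomisation that the drug is expected to cut to about 10 against 30, and the planned baseline adjustment does not restore comparability. Under the stated assumptions the set-point artefact is 0.13 to 0.60 log10, with a worst case of 1.09 SD. It is zero without selection, and its direction cannot be known in advance. The worst-case figure also assumes a normal set point and that tenofovir infections are a subset of those that would occur on placebo. No size can be given for resistance or CD4 from these figures.

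The efficacy hypothesis, the 40-endpoint design and the stopping rules all rest on seroconversion and are untouched. This is a cheap improvement to secondary objectives, not a flaw in the trial's main conclusion.

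**What to change.** In sections 6.2 and 7.2:

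- **Resistance.** Make the between-arm comparison the rate of resistant infections per person-year among all randomised participants, using the resistance test that section 10.3.7 already requires. This keeps the randomisation and measures the net burden, including infections averted. Report the proportion resistant among the infected as description.
- **Set point and CD4.** Label the infected-only differences as descriptive and conditional on infection. As a sensitivity analysis, report selection-bias bounds under the assumption that tenofovir infections are a subset of those that would occur on placebo. Compare the tenofovir values with the highest and then the lowest fraction of placebo values, where the fraction is the estimated ratio of infections (1/3 at 10 v 30). Do not require the bounds to exclude zero before a difference is discussed.

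No new visits, specimens or participants are needed. The cost is a little more analysis code and more cautious secondary conclusions. With about 10 v 30 infections the bounds will be wide, and a rate built on few resistant infections will be imprecise.
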